### Exclusion criteria

Participants meeting any of the following criteria will be excluded: (1) polycystic ovary syndrome, hyperprolactinemia, hyperandrogen, hypothyroidism, and other endocrine diseases which may inhibit ovulation; (2) DOR caused by iatrogenic factors (such as pelvic surgery, radiotherapy or chemotherapy, uterine artery embolism, drugs such as hormones or immunosuppressants); (3) participants who have taken hormone drugs in recent 3 months, such as estrogen, contraceptive, and glucocorticoids; (4) the score of Self-Rating Anxiety Scale (SAS) greater than 70; and (5) serious cardiovascular, cerebral, liver or kidney diseases, cancer, or psychiatric disease.

### Randomization and blinding

This trial will use the central randomization system provided by the Institute of Basic Research in Clinical Medicine of CACMS. Eligible participants will be randomly assigned to acupuncture or control groups in a 1:1 ratio. The randomization scheme and its related parameters protected by a strict viewing permission will be kept as blind code by a member of staff who is not involved in this study. The allocation sequence will be computer-generated. Acupuncturists will be responsible for randomization. They will obtain a random number and group assignment after entering gender and birthday of eligible participants into the central randomization system over cellphone or web. Participants, outcome assessors, and statisticians will be blind to treatment allocation during the whole study. Acupuncturists will not take part in the outcome assessment. Emergency unblinding is generally not required when serious adverse event (SAE) occurs. Unblinding during the trial will be permissible when acupuncture may affect the choice of treatment for SAE.

### Interventions

In this trial, *Hwato* disposable needles of different specifications (0.25 × 25 mm, 0.25 × 40 mm, and 0.30 × 75 mm) and SDZ-III electroacupuncture (EA) apparatus (Suzhou Medical Appliance, Jiangsu, China) will be used. Interventions in both groups will be administered by three acupuncturists who are registered practitioners of traditional Chinese medicine (TCM) and have at least 3 years’ clinical experience in acupuncture practice. Acupuncturists will receive training on study protocol and standard acupuncture manipulation before study initiation.

### Acupuncture group

The protocol for this group is based on clinical experience of the corresponding author [18]. It consists of two groups of acupoints: group 1 (in supine position), GV20 (Baihui), GV24 (Shenting), GB13 (Benshen), CV12 (Zhongwan), ST25 (Tianshu), CV4 (Guanyuan), KI12 (Dahe), EX-CA1 (Zigong), SP6 (Sanyinjiao), and LR3 (Taichong), and group 2 (in prone position), BL23 (Shenshu), BL33 (Zhongliao), and KI3 (Taixi). All the acupoints will be located according to the “WHO Standard Acupuncture Point Locations in the Western Pacific Region” [19]. These two groups of acupoints will be used alternatively with acupoints of group 1 as initial treatment. GV20, GV24, and GB13 will be needled with transverse insertion for 10 to 20 mm. LR3 will be inserted towards the direction of KI1 (Yongquan) for 10 to 20 mm. BL33 will be needled deeply into the third posterior sacral foramina for 60 to 70 mm. Other acupoints will be needled perpendicularly for 30 to 40 mm. Each acupoint is required to obtain deqi sensation (soreness, numbness, distention, heaviness, etc.), and if needed, needle manipulation techniques (like lifting, thrusting, or twirling the needle, etc.) can be applied to promote qi arrival. For acupoints of group 2, paired alligator clips from the EA apparatus will be connected to homolateral BL23 and BL33 with a dilatational wave and a current intensity that patients can tolerate. Participants will receive 3 sessions of acupuncture treatment per week (ideally every other day) for 12 weeks. Each acupuncture session will last for 20 min.

### Control group

In this trial, we will use superficial acupuncture in the same acupoints with the acupuncture group as sham control. All acupoints in this group will be needled into skin for approximately 1 to 3 mm with transverse insertion for GV20, GV24, and GB13 and perpendicular insertion for other acupoints. No manipulation will be administered after needle insertion to avoid deqi. When acupuncturing on the acupoints of group 2, participants will be informed to receive minor EA stimulation. The EA parameters will be the same as in acupuncture group, but electricity output will be the smallest possible one that participant agrees, and the final output should not induce visible needle shivering. The duration and frequency of the control group will be the same as in the acupuncture group.

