### Participants

A total of 120 patients with DOR will be recruited from outpatients of acupuncture and moxibustion hospital of CACMS via hospital poster, WeChat (a free popular social application in China) or network advertisement. Two staff members who are responsible for participant recruitment will conduct the consenting process in a separate clinic room in our hospital. Participants will be informed of details of the study which includes but is not limited to the objectives, interventions, potential benefits, and risks. Should the participants agree to join the study, they are required to submit a signed informed consent form.

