### Permitted and prohibited concomitant treatments

All participants will be treated individually and separately from other participants to prevent communication between groups. Participants will be prohibited from taking any forms of medicine for DOR, such as sexual hormones, contraceptives, Chinese herbs, and Chinese patent medicine. Participants will be discouraged to start an IVF cycle during intervention period. Nonetheless, after completing the first 4 weeks of the intervention period, participants are allowed to terminate this trial for the initiation of an IVF cycle if required. For treatment or IVF cycles that participants have already taken, relevant information will be documented in detail.

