### Measurements

#### Outcome measures

The primary outcome is the change of AFC from baseline to week 12. The differences between groups will be assessed. AFC is the number of visible ovarian follicles with a mean diameter of 2–10 mm observed during transvaginal ultrasound performed on menstrual cycle days 2–5. The number of antral follicles correlates with quantity of remaining follicles and with the ovarian response during COS. A low AFC is associated with poor response to ovarian stimulation during IVF.

Secondary outcomes are listed as follows.

(1) The mean change from the baseline in serum basal FSH, LH, and E2 will be compared between groups at week 12 and week 24.

Basal serum levels of FSH, LH, and E2 are measured on days 2–4 of the menstrual cycle. Basal FSH is commonly used to assess ovarian reserve, and high values greater than 10 IU/L are related with DOR and poor response to ovarian stimulation. An elevated basal estradiol level (greater than 50 pg/ml) in the early follicular phase indicates reproductive aging and hastened oocyte development.

(2) The mean change from baseline in serum AMH will be compared between groups at week 12 and week 24.

AMH is produced by the granulosa cells of primary, preantral, and antral follicles of 2–6 mm in diameter. It is a good predictor of oocyte quantity. A decrease of AMH indicates oocyte depletion. Since the level of AMH is fairly stable within and between menstrual cycles, it can be measured on any day of the cycle.

(3) The mean change from baseline in AFC at week 24 will be compared between groups.

(4) Change in the length of menstrual cycle at weeks 12 and 24. The length of menstrual cycle is divided into 3 categories: normal, antedated, or delayed menorrhea. The proportion of each category will be compared between groups at weeks 12 and 24.

(5) The mean change from baseline in the score of Self-Rating Anxiety Scale (SAS) will be compared between groups at weeks 12 and 24.

SAS is a self-rating scale for measuring the presence and severity of anxiety [20]. It consists of 20 items with 4 possible responses: (1) never, (2) rarely/sometimes, (3) frequently, and (4) always. The standard score is the integer part of the raw score (the sum of the 20 items) multiplied by 1.25. A higher score denotes more serious anxiety symptoms. In this trial, we will use a validated Chinese version of SAS [21].

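### Control participants are told that their electroacupuncture is minor, with no matching statement for the acupuncture group; this arm-specific wording may weaken participant blinding.

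*Protocol article*

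**What the plan says.** Three sections of the protocol article bear on this.

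- Randomization and blinding: "Participants, outcome assessors, and statisticians will be blind to treatment allocation during the whole study". The same section has the acupuncturists obtain the group assignment from the central system, so the people delivering treatment know the arm.
- Acupuncture group: at the second set of acupoints, EA is delivered "with a dilatational wave and a current intensity that patients can tolerate". Nothing is reported about what the participant is told.
- Control group: at the same acupoints, "participants will be informed to receive minor EA stimulation". The section adds that "electricity output will be the smallest possible one that participant agrees, and the final output should not induce visible needle shivering".

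Two other sections show where a participant's belief about her treatment could matter. Under Outcome measures, "SAS is a self-rating scale for measuring the presence and severity of anxiety", and it is compared between groups at weeks 12 and 24. Under Permitted and prohibited concomitant treatments, once the first 4 weeks of treatment are complete, "participants are allowed to terminate this trial for the initiation of an IVF cycle if required".

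**The concern.** A sham-controlled trial keeps the spoken information the same in both arms so that it carries no signal about allocation. Here the only printed statement to participants about EA strength is attached to one arm, and it describes that arm's stimulation as small. A woman who knows from consent that two forms of treatment are being compared could take it as a hint.

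Two things are at stake. The SAS is rated by the participant, so what she believes about her treatment can enter the score directly. The choice to leave for IVF is also hers, and a woman who thinks she is getting the lesser treatment has more reason to leave. On the SAS, such a belief would tend to favour acupuncture. The limitations paragraph in the Discussion considers only the opposite direction, that the sham control may produce a false negative result.

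**Working it through.** The plan gives no figure on this point, so the check is mainly a comparison of text.

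**1. Is the statement arm-specific as printed?** Yes. It stands in the Control group section and has no counterpart in the Acupuncture group section, and no section gives wording common to both arms. Both sections imply some exchange with the participant when the current is set: one sets it to what she tolerates, the other to the least she agrees to. The exchange itself is therefore not peculiar to the sham. The description of the stimulation as minor is.

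**2. Does it disclose the arm?** Not by itself. It works as a cue only if the participant knows that a stronger version exists. The Participants section says "Participants will be informed of details of the study which includes but is not limited to the objectives, interventions, potential benefits, and risks", so the interventions are described at consent, but how they are described is not shown.

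**3. How often could it be heard?** Inputs from the Acupuncture group section, which the Control group section adopts for frequency and duration: 3 sessions a week for 12 weeks, with two sets of acupoints alternating from set 1.

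- Sessions: 3 × 12 = 36
- Sessions with set 2 (EA): 36 / 2 = 18

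The text does not say whether the statement is made once or at each of these, so the range is 1 to 18.

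**4. Which outcomes can it reach?**

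- SAS: directly, because it is self-rated.
- AFC at week 12: not directly. It is an ultrasound count, and outcome assessors are stated to be blind. An indirect route exists if departures for IVF differ by arm. Multiple imputation on all randomized participants limits this, but does not by itself remove bias if leaving depends on an unrecorded belief about treatment.

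**5. Illustration for the SAS, by assumption only.** Suppose there is no true effect and belief alone shifts the group difference by d standard deviations. With n per group and z = d × √(n/2), the two-sided 5% test rejects with probability Φ(−1.96 + z) + Φ(−1.96 − z), by the normal approximation. The values of n are the 50 and 60 per group in the Sample size section. The values of d are assumed and come from no source.

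| d (assumed) | n = 50: z | rejects | n = 60: z | rejects |
|---|---|---|---|---|
| 0.1 | 0.50 | 7.9% | 0.55 | 8.5% |
| 0.2 | 1.00 | 17.0% | 1.10 | 19.5% |
| 0.3 | 1.50 | 32.3% | 1.64 | 37.6% |

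This shows how sensitive the test is to a small shift. It does not estimate the shift in this trial.

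**The case against.** The strongest reply is that the contrast rests partly on silence. A journal article condenses the protocol, and the acupuncture group may well be told something comparable that was not printed. The sentence may even protect the sham, by giving a woman who feels little current a reason for it. Participants are treated individually, so they have no one to compare with. Needle depth already differs sharply (about 1 to 3 mm against as much as 60 to 70 mm), as does deqi, which is sought in one arm and avoided in the other. A single adjective may add little to that.

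Much of this stands. It rules out several stronger readings that a reader might infer:

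- *That participants are unblinded.* The word does not name an arm, and the consent text is not shown.
- *That each control participant receives the cue 18 times.* That is the number of EA sessions; repetition is not stated.
- *That patients will recognise the cue because acupuncture is well known in China.* The Discussion uses that point to explain why a placebo is hard to run, and says nothing about patients judging EA strength.
- *That the primary outcome is biased.* The only route is indirect. Data management and quality control provides for recording reasons and as much outcome data as possible for those who discontinue.
- *That blinding is never checked.* An article may leave a treatment-guess item to the full protocol or the case report form.

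What the reply does not remove is the printed instruction itself. It is given for one arm, by staff who know the allocation, and it sits beside an unqualified claim of participant blinding. Unlike depth and deqi, which belong to the comparison, the wording can be made the same at almost no cost.

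**Conclusion.** The point holds as a risk to blinding, not as a demonstrated failure. As written, the spoken information about EA differs by arm and may weaken the participant blinding that the protocol claims. The exposure is mainly on the SAS, a secondary outcome, and less directly on unequal departure for IVF after week 4. The AFC reading is not directly affected.

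The size of any bias cannot be derived from the document. The conclusion assumes that the acupuncture group is not given the same statement and that consent tells women enough for the word to carry meaning. If the full protocol shows one common statement, the point reduces to a correction of the article's text.

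**What to change.** Reconcile the Randomization and blinding, Acupuncture group and Control group sections by giving one identical statement about EA in both arms. It should be silent on strength and true for every participant, for example that what people feel varies. That still prepares a woman who feels little. Stimulation settings stay as they are. If a common statement is already in use, print it under both arms.

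A single treatment-guess question at week 12, reported by arm, is an optional addition that would show how far blinding held.

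The cost is one script line, plus one case report form item if the question is added. The Trial status section says recruitment is still open, so the change can protect only later participants, and its date should be recorded. The sensory differences between the arms remain, so this removes an avoidable cue and does not secure blinding on its own.

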### Permitted and prohibited concomitant treatments

All participants will be treated individually and separately from other participants to prevent communication between groups. Participants will be prohibited from taking any forms of medicine for DOR, such as sexual hormones, contraceptives, Chinese herbs, and Chinese patent medicine. Participants will be discouraged to start an IVF cycle during intervention period. Nonetheless, after completing the first 4 weeks of the intervention period, participants are allowed to terminate this trial for the initiation of an IVF cycle if required. For treatment or IVF cycles that participants have already taken, relevant information will be documented in detail.

### Discontinuation of the intervention

The intervention will be terminated when (1) SAE or pregnancy occurs and (2) participants ask to quit the trial or withdraw their informed consents.

### Measurements

#### Outcome measures

The primary outcome is the change of AFC from baseline to week 12. The differences between groups will be assessed. AFC is the number of visible ovarian follicles with a mean diameter of 2–10 mm observed during transvaginal ultrasound performed on menstrual cycle days 2–5. The number of antral follicles correlates with quantity of remaining follicles and with the ovarian response during COS. A low AFC is associated with poor response to ovarian stimulation during IVF.

Secondary outcomes are listed as follows.

(1) The mean change from the baseline in serum basal FSH, LH, and E2 will be compared between groups at week 12 and week 24.

Basal serum levels of FSH, LH, and E2 are measured on days 2–4 of the menstrual cycle. Basal FSH is commonly used to assess ovarian reserve, and high values greater than 10 IU/L are related with DOR and poor response to ovarian stimulation. An elevated basal estradiol level (greater than 50 pg/ml) in the early follicular phase indicates reproductive aging and hastened oocyte development.

(2) The mean change from baseline in serum AMH will be compared between groups at week 12 and week 24.

AMH is produced by the granulosa cells of primary, preantral, and antral follicles of 2–6 mm in diameter. It is a good predictor of oocyte quantity. A decrease of AMH indicates oocyte depletion. Since the level of AMH is fairly stable within and between menstrual cycles, it can be measured on any day of the cycle.

(3) The mean change from baseline in AFC at week 24 will be compared between groups.

(4) Change in the length of menstrual cycle at weeks 12 and 24. The length of menstrual cycle is divided into 3 categories: normal, antedated, or delayed menorrhea. The proportion of each category will be compared between groups at weeks 12 and 24.

(5) The mean change from baseline in the score of Self-Rating Anxiety Scale (SAS) will be compared between groups at weeks 12 and 24.

SAS is a self-rating scale for measuring the presence and severity of anxiety [20]. It consists of 20 items with 4 possible responses: (1) never, (2) rarely/sometimes, (3) frequently, and (4) always. The standard score is the integer part of the raw score (the sum of the 20 items) multiplied by 1.25. A higher score denotes more serious anxiety symptoms. In this trial, we will use a validated Chinese version of SAS [21].

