### Inclusion criteria

Participants who meet the following inclusion criteria will be included: (1) female, aged 18–40 years; (2) meet any of the following three items in both tests with an interval of at least 4 weeks: (a) 10 IU/L < FSH < 20 IU/L, tested on days 2–4 of menstrual cycle; (b) anti-Müllerian hormone (AMH) < 1.1 ng/mL; (c) antral follicle count (AFC) < 5–7, tested on days 2–4 of menstrual cycle; and (4) voluntarily join the research and sign the informed consent.

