#### Statistical analysis

SPSS version 20.0 (SPSS Inc., Chicago, USA) will be used for statistical analysis. According to the intention-to-treat (ITT) principle, statistical analysis will be conducted on all randomized subjects. Missing data will be imputed using multiple imputation method. Continuous data will be presented with mean and standard deviation, or median and interquartile range, while categorical data will be presented with number and percentage. For comparison with the baseline, a paired t-test or non-parametric test will be used for continuous data, and nonparametric test for categorical data. Comparisons between groups will be analyzed using the independent *t* test or non-parametric test for continuous data, chi-square test or Fisher exact test for categorical data, and nonparametric test for ranked data. All statistical tests will be two-sided, and *p* < 0.05 will be considered statistically significant.

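### FSH, LH, E2 and AMH are compared as raw changes without baseline adjustment; an ANCOVA on the log scale would use data already collected and may be more precise (secondary outcomes only)

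*Protocol article*

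**What the plan says.** Under Outcome measures, secondary outcome (1) reads "The mean change from the baseline in serum basal FSH, LH, and E2 will be compared between groups at week 12 and week 24". Secondary outcome (2) reads "The mean change from baseline in serum AMH will be compared between groups at week 12 and week 24". Both are absolute changes in natural units.

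Under Statistical analysis, the between-group method is "Comparisons between groups will be analyzed using the independent *t* test or non-parametric test for continuous data". The summary rule is "Continuous data will be presented with mean and standard deviation, or median and interquartile range". Missing data are to be multiply imputed. No logarithm, ratio, geometric mean or baseline covariate is mentioned anywhere.

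Table 1 shows that all four hormones are measured at screening, week 12 and week 24, so every randomised woman should have a baseline value.

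Under Inclusion criteria, women must "meet any of the following three items in both tests with an interval of at least 4 weeks". Two of the items are "10 IU/L < FSH < 20 IU/L" and "anti-Müllerian hormone (AMH) < 1.1 ng/mL"; the third is a low antral follicle count (AFC). Because one item is enough, neither hormone limit applies to every woman.

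**The concern.** Two features of the stated analysis can waste information.

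**Baseline.** A comparison of change scores subtracts the baseline with a fixed weight of one. ANCOVA estimates that weight from the data. When baseline and follow-up are imperfectly correlated, ANCOVA leaves less residual variance.

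**Scale.** Concentrations cannot fall below zero. If acupuncture shifts a hormone by a roughly constant percentage and values are right-skewed, the raw change varies with the woman's level and the comparison is noisier than on the log scale. Ranking the raw changes limits the pull of extreme values but keeps the dependence on level. It also gives no estimate of the mean change that the outcomes promise.

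The Discussion section says that hormones, AMH and AFC will be considered together in judging ovarian reserve, and the sample size was set for AFC only. A real proportional hormone effect could therefore be missed when the same data, analysed more efficiently, would show it.

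**Working it through.** **The plan's own figure.** The sample size uses an AFC difference of 2.25 − 0.80 = 1.45 and a standard deviation of 2.22, with 90% power and two-sided 5%:

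n per group = 2 × (1.96 + 1.2816)² × 2.22² / 1.45² = 2 × 10.507 × 4.9284 / 2.1025 = 49.3, so 50.

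The stated 50 per group reproduces (power at 50 is 90.4%). It concerns AFC alone; no figure is given for the hormones.

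**Assumptions for the hormones (none are in the protocol).** Log-normal values; log-SD 0.3 to 0.8; log-scale correlation ρ between baseline and follow-up of 0.6 to 0.8; 50 women per arm; a proportional effect set for about 80% power on log change:

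log ratio = (1.96 + 0.8416) × log-SD × √(2(1 − ρ)) × √(2/50).

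For log-SD 0.5 and ρ = 0.6 this is 2.8016 × 0.5 × 0.894 × 0.2 = 0.251, a ratio of 1.29 or its inverse.

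**Gain from baseline adjustment on the log scale, by formula.** Variance under ANCOVA relative to change score = (1 − ρ²) / (2(1 − ρ)) = (1 + ρ)/2, which is 0.80 at ρ = 0.6 and 0.90 at ρ = 0.8. Approximate power:

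- ρ = 0.6: Φ(2.8016/√0.80 − 1.96) = Φ(1.17) = 88%
- ρ = 0.8: Φ(2.8016/√0.90 − 1.96) = Φ(0.99) = 84%

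**Simulated power by direction** (ρ 0.6 to 0.7, 3,000 trials per setting). A fall is the relevant direction for FSH and LH, since the Background cites decreases in both after acupuncture.

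| Direction, log-SD | t test, raw change | Rank test, raw change |
|---|---|---|
| Rise, 0.3 | 78-80% | 78% |
| Rise, 0.5 | 75-76% | 77-78% |
| Rise, 0.8 | 64-66% | 75% |
| Fall, 0.3 | 72-74% | 71-74% |
| Fall, 0.5 | 64-65% | 67-69% |
| Fall, 0.8 | 50-51% | 64% |

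In the same settings the t test on log change has 78-81% and log ANCOVA 84-88%.

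**Full range** (ρ 0.6 to 0.8, log-SD 0.3 to 0.8, both directions): raw-change t test about 50-78%, rank test 62-81%, raw ANCOVA 62-85%, log ANCOVA 81-89%. Type I error is near 5% for every method. A repeat run with 4,000 trials per setting fell inside these ranges.

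**Separating the two sources.** At log-SD 0.5, ρ = 0.6 and a fall, power is about 64% for the raw-change t test, 80% for raw ANCOVA and 87% for log ANCOVA. Baseline adjustment supplies 80 − 64 = 16 points and the log scale 87 − 80 = 7. In the repeat run, moving from raw to log ANCOVA added about 2 to 3 points at log-SD 0.3 and 15 to 19 at log-SD 0.8.

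**The case against.** **The model is assumed.** The protocol reports no standard deviation, range, skewness or correlation for any hormone. The simulation uses log-normal data with a proportional effect, which is the setting where a log analysis does best. This stands: the figures show what would follow if the data are like that, not that they are. A reader might infer from the any-one-of-three entry rule that FSH or AMH will be widely spread and that a few extreme women will dominate the result. The rule shows only that the entry limits do not cap these markers for everyone; it says nothing about actual spread.

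**The plan already allows for skewed data.** It permits a rank test and medians with interquartile ranges. This stands in part. A rank test does limit domination by extreme values, and for a proportional rise it recovers most of the loss. For a fall it recovers less: 67-69% at log-SD 0.5 against 78-81% on log change.

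**Transformations and covariates belong in the analysis plan.** Silence on them would be no finding. Here, however, the article names both the effect measure and the between-group tests, so it states a method that can be compared with a better one. It remains true that mean change is the article's general wording, used for AFC and anxiety scores as well, and is neither an error nor a contradiction.

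**Only secondary outcomes are involved.** This stands. The sample size and primary comparison rest on AFC, and no decision rule is attached to the hormone p-values.

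**Conclusion.** The stated hormone analysis is valid but probably inefficient. It does not use the collected baseline as a covariate, and it uses a scale that costs power if effects are proportional and values right-skewed. Under the stated assumptions, power is about 50-78% (t test) or 62-81% (rank test), against 81-89% for log ANCOVA.

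A reader might attribute the whole gap to the raw scale. That would be wrong: raw ANCOVA already reaches about 62-85%, and once baseline is adjusted for, the log scale matters little at log-SD 0.3. The case for baseline adjustment needs little skewness; the case for logs depends on it. Nor do the documents support calling the planned tests biased or invalid, since type I error stays near 5%.

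The point is of low severity, confined to secondary outcomes (1) and (2). The primary AFC analysis is untouched.

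**What to change.** Before unblinding, amend secondary outcomes (1) and (2) and the Statistical analysis section to state that:

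- FSH, LH, E2 and AMH at weeks 12 and 24 are each analysed by ANCOVA of the log follow-up value, with treatment group and log baseline in the model.
- The result is reported as the ratio of geometric means, acupuncture to sham, with its 95% confidence interval.
- Multiple imputation for these outcomes is done on the same log scale.
- Raw mean change is kept as a descriptive summary.

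The cost is wording only: no new data, visits or participants. There are two small downsides. Results read as ratios rather than differences in natural units, and values below an assay limit need one fixed substitution value, stated in advance.
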